### Monitoring Days 2–5 Post hAEC Transplantation

The following will be performed after 24 h of therapy:

• Post infusion days 2–4: daily telephone contact to assess overall status• Post infusion day 5: clinical assessment including open ended questioning to ascertain any adverse events, recording concomitant medications and measuring FBE, UEC, LFT, AST, CRP, INR. A 10 ml serum sample will be obtained for storage.Post infusion week 8 for cohorts 1 and 2, week 12 for cohort 3, week 16 for cohort 4: Routine laboratory tests (as for day 5), Fibroscan and HVPG measurements will be performed and a serum sample (10 ml) obtained for storage.

### Long-Term Follow-Up

All study subjects will be followed 6-monthly for a minimum of 2 years with abdominal ultrasounds and routine laboratory tests (FBE, LFT, UEC, INR, AFP). This testing regimen is the standard of care for cirrhotic patients who require lifelong surveillance for hepatocellular carcinoma.

## Outcomes

### Primary (Assessment of Safety)

(a)Local skin reactions – extravasation, erythema, edema.(b)Anaphylaxis – acute deterioration of respiratory, cardiovascular parameters:Respiratory deterioration – dyspnoea, hypoxema, any requirement for supplemental oxygen or mechanical ventilation.Cardiovascular deterioration – hypotension, hypertension, bradycardia, tachycardia, rhythm abnormalities.(c)Infection – clinical signs, laboratory evidence (increase in CRP, white cell counts, bacterial/viral growth on sterile cultures).(d)Features of rejection as evidenced by impairment in hepatic or renal parameters.Hepatic – new onset jaundice, elevation of hepatic enzymes, coagulation dysfunction – thrombocytopenia, increase in INR.Renal – decrease in eGFR.

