## Inclusion Criteria

• Female or male• Age ≥ 18 years, ≤ 70 years

Aetiology of liver disease, one or more of:

• Non-alcoholic fatty liver disease• Alcohol related liver disease – abstinent for at least 3 months• Hepatitis C virus infection (treated or not treated)• Hepatitis B virus infection (on nucleoside analogs with normal ALT and HBV DNA) or inactive phase• HIV co-infection with HCV/HBV with virological suppression > 12 months• Cryptogenic cirrhosis• Hemochromatosis

Cirrhosis, defined as one of:

• Liver biopsy confirming histological features of cirrhosis• Transient elastography (Fibroscan) > 14.8 kPa• FIB 4 > 3.25• Clinical and radiological features that in the opinion of the investigator are consistent with a diagnosis of cirrhosis• Compensated cirrhosis defined by HVPG 6–10 mmHg.

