## Design and Conduct of the Study

### hAEC Retrieval and Preparation

Healthy pregnant mothers delivering at term gestation will be approached and consented for donation of their amniotic membranes. The donor mothers will be screened for all viral and other infections (CMV, HIV, Hepatitis B and C virus – similar to blood transfusion donors) on day of delivery. These investigations will be repeated 3 months later again to exclude pathogens that might have been in incubation during delivery. hAECs will be isolated in a GMP-certified Biospherix Unit housed in the Monash Health Translation Precinct – Translational Research Facility (MHTP TRF) and stored in a secure and dedicated liquid nitrogen dewar until the donor has been cleared for use.

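### The primary infection outcome names no specific test for the donor viruses the protocol lists, and no viral assay is listed for recipients after infusion

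*Protocol article*

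**What the plan says.** All references are to the protocol article.

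- **Outcome.** Outcomes, Primary (Assessment of Safety), item (c), evidences infection by clinical signs and by "laboratory evidence (increase in CRP, white cell counts, bacterial/viral growth on sterile cultures". Item (d) of the same list infers rejection from worsening liver or kidney measures, including new jaundice and raised liver enzymes.
- **Donors.** Under hAEC Retrieval and Preparation, donor mothers are "screened for all viral and other infections (CMV, HIV, Hepatitis B and C virus". The section adds: "These investigations will be repeated 3 months later again to exclude pathogens that might have been in incubation during delivery". Cells are "stored in a secure and dedicated liquid nitrogen dewar until the donor has been cleared for use".
- **Recipients after infusion.** Day 5 consists of a clinical assessment and "measuring FBE, UEC, LFT, AST, CRP, INR. A 10 ml serum sample will be obtained for storage". The visit at week 8 (cohorts 1 and 2), 12 (cohort 3) or 16 (cohort 4) repeats the day-5 tests and stores serum. Long-Term Follow-Up lists blood count, liver and renal tests, INR and AFP every 6 months for at least 2 years.
- **Recipients before infusion.** Inclusion Criteria admit "Hepatitis C virus infection (treated or not treated", as well as controlled or inactive hepatitis B and suppressed HIV co-infection. Exclusion Criteria set a limit on HBV DNA and exclude uncontrolled HIV viraemia.

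**The concern.** The donor section shows which transmissible agents the protocol has in mind, and Expected Outcomes likens the theoretical risks to those of blood transfusion. The recipient outcome meant to capture such an event is built from other evidence: clinical signs, two non-specific markers and culture. A recipient who silently acquired one of the named viruses could pass every listed visit without meeting item (c). If the virus affected the liver, the first trace would probably be a rise in liver enzymes, which item (d) labels rejection.

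This is a first-in-adult trial of allogeneic cells whose purpose is safety. A report of no infections would then mean that none was noticed, not that the named viruses were looked for.

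**Working it through.** The point concerns how an outcome is measured, so there is no plan figure to reproduce. The check sets the definition beside every itemised test list for recipients.

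| Occasion (section) | Viral assay listed | Culture listed | CRP listed | Serum stored |
|---|---|---|---|---|
| Baseline (Screening to Day of Treatment) | none | none | yes | yes |
| Day 5 (Monitoring Days 2–5) | none | none | yes | yes |
| Week 8/12/16 (same section) | none | none | yes, as for day 5 | yes |
| 6-monthly (Long-Term Follow-Up) | none | none | no | not stated |

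Monitoring on Day of Treatment adds stored serum at 12 and 24 h. Table 2 says only blood tests, serum sample and biomarkers, without detail.

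**Step 1, count.** Lists with an HIV, HBV, HCV or CMV assay: 0 of 4 overall, 0 of 3 after infusion. Culture is part of the definition but appears in no list, so the one element of item (c) that refers to viruses is not scheduled at any visit.

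**Step 2, before infusion.** The HBV DNA limit and the HIV viraemia criterion cannot be applied without viral results in the patients concerned. Hepatitis C appears only as an aetiology, and CMV is not mentioned for recipients. Some baseline information is therefore implied, but not a uniform baseline for all four viruses.

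**Step 3, timing of the last stored sample.** Under Study Design, the last infusion falls at week 0 (cohorts 1 and 2), week 4 (cohort 3, day 28) or week 8 (cohort 4, day 56). The gap to the stored sample is 8 − 0 = 8, 12 − 4 = 8 and 16 − 8 = 8 weeks, in line with the last column of Table 2. The protocol's own donor retest interval is 3 months, about 13 weeks. A method with a long window, such as serology, would therefore stop about 13 − 8 = 5 weeks short of it. A 6-monthly draw, even if counted from the first infusion, falls at about 26 − 8 = 18 weeks after the last infusion in cohort 4, which clears 13 weeks.

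**Step 4, size of the fix.** Baseline plus week 8/12/16: 12 × 2 = 24 panels. With the first 6-monthly draw: 12 × 3 = 36 panels.

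**Step 5, what a clean result would show.** With zero events in n assessable patients, the one-sided 95% upper limit is 1 − 0.05^(1/n). For n = 12 this is 1 − 0.05^(1/12) = 0.22. A recipient who already carries a virus is not assessable for acquiring it, so n falls. The documents give no case mix. If, as an assumption for illustration, half were carriers of a given virus, n = 6 and the limit is 1 − 0.05^(1/6) = 0.39.

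**The case against.** The strongest reply has five parts.

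- **Control sits with the donor.** Two rounds of donor testing, with cells held until clearance, are the main protection. This stands and keeps the absolute risk low. It lowers the chance of an event but does not measure the recipient outcome.
- **The printed lists are abbreviated.** The baseline list omits HVPG and ultrasound, which Table 2 marks at screening, and the HBV DNA that eligibility needs. An article condenses a fuller protocol, which may hold a virology panel. This stands as to the lists, and their silence alone would not be a finding. But the article does print the outcome definition, and as printed a positive viral assay is not among the laboratory evidence. One could read the bracketed items as examples only; the text does not say so.
- **Other routes exist.** Clinical signs and viral growth are in item (c), abnormal laboratory findings count as adverse events, and liver tests recur for at least 2 years. It is therefore too strong to infer that the outcome cannot detect these viruses. What the text supports is that it names no specific test for them. Review by the monitoring board is described for serious events, and an isolated enzyme rise need not be one.
- **Pre-infusion results exist.** A reader might infer that recipients have no viral test before infusion. The eligibility criteria contradict that for HBV DNA and HIV viraemia. Stored baseline serum also permits later look-back, although no such assay is planned in the text.
- **Twelve patients cannot prove absence of transmission.** True, as step 5 shows, and the protocol does not claim it. The same holds for every safety outcome here, and it is no reason to leave the named viruses without a named test.

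**Conclusion.** The point holds in limited form. The infection outcome names no specific test for the four donor viruses that the protocol lists, 0 of 3 itemised post-infusion lists contain one, baseline status is implied for only some viruses, and item (d) could draw a transmitted hepatitis into rejection. The loss is in interpretation: a report of no infection would carry little information about these agents.

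Two further readings should be avoided. The documents do not show a material risk of transmission, given the donor testing and quarantine. Nor do they show that many recipients will already be infected: fatty liver, alcohol-related, cryptogenic and hemochromatosis aetiologies are also eligible, and no case mix is given. Carriers are merely allowed, which is enough to require comparison with baseline.

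The conclusion assumes that the printed definition is the operative one. It also takes from general laboratory knowledge, not from the documents, that HIV, HBV and HCV are not routinely found by culture, whereas CMV can be grown. It does not depend heavily on this, since no culture is scheduled either.

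**What to change.** 1. In item (c) of the primary outcomes, add: *new HIV, HBV, HCV or CMV detection by nucleic-acid test (with serology where useful), compared with the pre-infusion sample*.
2. Assign these assays to the serum already stored at baseline and at week 8/12/16: 24 panels, with no new visit or procedure. Nucleic-acid testing is preferred because the last stored sample falls about 8 weeks after the last infusion. If serology is relied on, add the first 6-monthly blood draw (36 panels in all); no storage is stated for that draw, so it needs an extra tube.
3. In item (d), classify a liver enzyme rise as rejection only after these viral results have been checked.
4. For a virus that a recipient already carries, report new acquisition as not assessable, and give the number of assessable patients for each virus.

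The cost is a small laboratory charge and a line in the consent form.

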### Expected Outcomes

It is expected that the intravenous administration of hAECs in adults with compensated or decompensated cirrhosis will be generally safe. There is a theoretical risk of local and systemic side effects akin to those following blood transfusions. It is extremely unlikely that there will be development of rejection phenomena or long term tumor formation.

## Statistical Analysis

There is no planned formal statistical analysis of this phase I trial, but descriptive and inferential statistical analysis will be conducted as appropriate. Data emerging from the study will be used to develop statistical parameters for phases 2 and 3 studies. A data and safety monitoring board (DSMB) will be established to provide study oversight, peer review by an expert panel independent of the investigators to audit informed consent, research subject monitoring, study conduct, trial registration, and reporting.

## Consent

Informed written consent will be obtained from each patient who will retain the right to revoke consent at any time after inclusion in the trial without prejudice for future medical care.

## Data Collection and Analyses

Data will be collected prospectively and each individual patient will be monitored and outcomes reviewed following each administration of hAECs. If at any point, significant adverse events are noted directly or indirectly attributable to the hAECs, further recruitment of patients will be stopped pending review by the DSMB and investigators.

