## Methods and Analysis

### Study Design

In this open label phase 1 study, the safety and tolerability of hAEC transplantation will be examined in 12 patients with compensated cirrhosis (**Figure 1**). They will be divided into four cohorts. Each cohort will include three patients treated sequentially (patient 1, then patient 2, then patient 3). Each patient will be observed for serious adverse events (SAEs) for 5 days post intravenous (IV) hAEC infusion before the next patient is enrolled. In Cohort 1, three patients will receive hAEC (0.5 × 10^6^/kg) as a single IV injection. If no SAE occur within 5 days of the last infusion in Cohort 1, a further three patients will be sequentially enrolled in Cohort 2 and receive a higher hAEC dose (1.0 × 10^6^/kg) as a single IV injection. If no SAE occur within 5 days of the last infusion in Cohort 2, a further three patients will be sequentially enrolled in Cohort 3 and receive the same hAEC dose as Cohort 2 (1.0 × 10^6^/kg) as a single IV injection at days 0 and 28. If no SAE occur within 5 days of the last infusion in Cohort 3, a further three patients will be sequentially enrolled in Cohort 4 and receive the same hAEC dose as Cohort 3 (1.0 × 10^6^/kg) as a single IV injection at days 0, 28, and 56 (**Table 1**).

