**FIGURE 1 F1:**
[figure not shown]
Studydesign.

**Table 1 T1:** Indicative minimal timeline.

**Cohort**/patient number	**C1**/1, 2, 3 (One infusion/patient)	**C2**/4, 5, 6 (One infusion/patient)
Week of study	0–8	12–20
**Cohort**/patient number	**C3**/7, 8, 9 (Two infusions/patient)	**C4**/10, 11, 12 (Three infusions/patient)
Week of study	24–52	44–76

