### Serious Adverse Event Reporting

All SAEs that occur after hAEC administration (whether or not considered related to hAEC) will be reported within 24 h to the DSMB. Promptly after the occurrence of the event, the treating physician would submit an initial written report of any SAE to the HREC. Any necessary follow-up will be submitted within a reasonable time thereafter.

The independent DSMB will review each SAE report and evaluate the relationship of the SAE to hAEC and determine a need for further action. If the discovery of a new adverse event related to hAEC raises concern over the safety of continued administration of the drug, the DSMB and PI will take immediate steps to notify the regulatory authorities, HREC and all physicians who have treated patients with hAECs.

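### The safety pause stops recruitment only, so it does not hold the repeat infusions of patients already enrolled in Cohorts 3 and 4

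*Protocol article*

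**What the plan says.** The stopping rule is a single sentence under Data Collection and Analyses. Its trigger is a significant adverse event attributable, directly or indirectly, to the cells. Its consequence is that "further recruitment of patients will be stopped pending review by the DSMB and investigators". The sentence before it says that each patient is monitored and that outcomes are reviewed after every administration.

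Study Design sets out the dosing: "the safety and tolerability of hAEC transplantation will be examined in 12 patients with compensated cirrhosis", in four cohorts, and "Each cohort will include three patients treated sequentially". Cohorts 1 and 2 have one infusion per patient and Cohort 3 has two (days 0 and 28). In Cohort 4 the cells are given "as a single IV injection at days 0, 28, and 56". The spacing rule reads: "Each patient will be observed for serious adverse events (SAEs) for 5 days post intravenous (IV) hAEC infusion before the next patient is enrolled". The next cohort opens if no SAE has occurred within 5 days of the previous cohort's last infusion.

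Serious Adverse Event Reporting sends every SAE to the DSMB within 24 h and adds: "The independent DSMB will review each SAE report and evaluate the relationship of the SAE to hAEC and determine a need for further action". If a newly found related event raises concern about continuing the product, the immediate step named there is to notify regulators, the ethics committee and treating physicians.

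**The concern.** A recruitment stop is enough for Cohorts 1 and 2, because no patient receives anything further after the first infusion. It is too narrow for Cohorts 3 and 4, where later doses are already scheduled when the event occurs. Between an attributable event and the DSMB's decision, an enrolled patient can come due for another dose of the product under review, and the stated rule does not withhold it. The patient who has just had the event is the one for whom a hold matters most, and the rule does not cover that patient. This is an allogeneic cell product in a first-in-adult study whose primary safety outcomes include anaphylaxis and features of rejection.

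**Working it through.** **Infusion counts** (Study Design; infusions per patient confirmed in Table 1)

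| Cohort | Patients | Infusions per patient | Infusions | Repeats after enrolment |
|---|---|---|---|---|
| 1 | 3 | 1 | 3 | 0 |
| 2 | 3 | 1 | 3 | 0 |
| 3 | 3 | 2 | 6 | 3 |
| 4 | 3 | 3 | 9 | 6 |
| Total | 12 | | 21 | 9 |

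The patient total matches the article's 12. The article gives no total for infusions. Repeats are 9/21 = 43%.

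**What each rule stops**

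- Pause under Data Collection and Analyses: recruitment.
- 5-day gates under Study Design: enrolment of the next patient or the next cohort.
- DSMB under Serious Adverse Event Reporting: whatever it decides after reviewing the SAE.

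None holds a day-28 or day-56 infusion while the review is pending. Patient 12's second and third infusions always follow the last enrolment, whatever the timetable, so the pause cannot affect them.

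**Doses outstanding in one pause**

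Table 1 ("Indicative minimal timeline") gives weeks 24–52 for Cohort 3 and 44–76 for Cohort 4, spans of 28 and 32 weeks. It does not say what the spans cover. Assume that they run to the last scheduled visit ("week 12 for cohort 3, week 16 for cohort 4") and that the three patients are evenly spaced:

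- Cohort 3: (28 − 12)/2 = 8 weeks between starts, against a 4-week dosing course.
- Cohort 4: (32 − 16)/2 = 8 weeks between starts, against an 8-week dosing course.

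Courses within a cohort then share at most one week. Just after a first infusion, 1 dose (Cohort 3) or 2 doses (Cohort 4) are outstanding, in one patient. This reading is approximate: the 8-week spans of Cohorts 1 and 2 would leave 8 − 8 = 0 weeks for staggering. Reading the spans as dosing only does not work either. Cohort 3 would then be dosing until week 52 while Cohort 4 opens at week 44, against the cohort gate.

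The upper bound comes from the 5-day minimum spacing, counted from each patient's first infusion (starts on days 0, 5 and 10). Just after day 10, 3 repeats are outstanding in Cohort 3, or 6 in Cohort 4. This is faster than Table 1.

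**When a dose falls due during review**

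For an event t days after an infusion with the next dose at day 28, the review must last at least 28 − t days:

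| t (days) | Review length needed (days) |
|---|---|
| 0 | 28 |
| 5 | 23 |
| 14 | 14 |
| 21 | 7 |

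Table 2 gives days 1, 30 and 60 instead, so the intervals become 29 and 30 days. The counts do not change.

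Review length is not stated. For assumed lengths of 7, 14 or 28 days, there are 9 × 28 = 252 patient-days ahead of a repeat dose. An event on 63 (25%), 126 (50%) or 252 (100%) of those days would leave that patient's next dose due before the review ends. These shares weight all days equally and are only illustrative. Events close to the infusion need the longer reviews, and the 100% follows from assuming a review as long as the dosing interval.

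**The case against.** The strongest reply is that other safeguards lie between doses. Outcomes are reviewed after each administration. Table 2 schedules a clinical assessment and blood tests on each infusion day and on day 5 after each infusion, and there is telephone contact on days 2–4. SAEs reach the DSMB within 24 h, and it can order action. An investigator would probably withhold the dose in practice. All this makes harm less likely, but these steps are monitoring or discretion, and none withholds a dose until the review is complete. The 24 h reporting also covers SAEs only, whereas the pause is triggered by significant adverse events, a term not tied to the SAE definition. For an attributable event that is significant but not serious, the recruitment stop may be the only stated consequence.

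A second reply is that an article condenses its protocol and may leave dose-withholding criteria to the full document. That would answer a complaint that a rule is missing. Here the article does state the rule, with trigger, consequence and reviewers, and the stated consequence is too narrow for the repeat-dose cohorts.

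A third reply is that 9 of 21 overstates the exposure. That is fair: it is a trial-wide total. On the indicative timeline one pause would usually involve 1 or 2 doses in one patient, and an event inside the 5-day window needs a review of at least 23 days before the next dose is due.

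**Conclusion.** The point holds. Followed as written, the automatic pause holds none of the 9 repeat infusions and has no effect once patient 12 is enrolled. Both statements follow from the stated rules and dose schedule without any timing assumption. How often the gap would matter does depend on assumptions: patient spacing, the day of the event and the unstated length of review. The likely exposure is small, 1 or 2 doses in one patient, rising to 3 or 6 only at the 5-day minimum spacing. It should be fixed because it concerns patient safety, the trial's primary objective, and the correction is cheap.

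**What to change.** In the stopping sentence under Data Collection and Analyses, widen the consequence to: *further recruitment and all further hAEC infusions, including repeat infusions in patients already enrolled, will be stopped*, pending the same review. Add that the DSMB decides whether a held dose is given late or omitted.

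Sample size and dose levels do not change. The cost is that a day-28 or day-56 dose may be late or missed, so a cohort may end with fewer than three patients on the full schedule. The HVPG visit would move with the last infusion, because Table 2 sets it 8 weeks afterwards. For example, a Cohort 4 patient whose day-56 dose is omitted would be due at week 4 + 8 = 12 instead of 8 + 8 = 16. The revised text should say which timing applies.
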